Research proposal for IRB approval

Effects of recruitment maneuver in patients undergoing robotic assisted radical prostatectomy	

2013. 7.

Seoul National University Bundang Hospital
 Department of Anesthesiology & Pain medicine

[name]

< Summary of proposal >

Title	Effects of recruitment maneuver in patients undergoing robotic assisted radical prostatectomy	
Background	- There is increasing attention for robotic assisted radical prostatectomy (RARP) for lower rates of complications and better surgical outcome.
- In RARP, the operative position should be a Trendelenburg head-down position of 30¡Æslope, which is much steeper than that of other surgeries. 
-The steep Trendelenburg head-down position and relatively long duration of CO2 pneumoperitoneum can result in an increased risk of intraoperative hypoxia and postoperative atelectasis. Furthermore, patients undergoing RARP are mostly elderly and the risk of pulmonary complications is increased. 
- Recently, positive end expiratory pressure(PEEP) and recruitment maneuver(RM) are commonly used during general anesthesia to improve oxygenation. It is known that using PEEP during laparoscopic procedures is beneficial, on the contrary benefit of RM is not established, especially in RARP. 	
Purpose	This study is designed to evaluate the efficacy of RM on intraoperative oxygenation, ventilatory mechanics, and postoperative pulmonary complications.	
Method	- A total of 60 patients, aged 60-80 years with ASA class 1 or 2, scheduled for elective RARP under general anesthesia will be enrolled and randomly allocated to two groups.
- Positive end expiratory pressure (PEEP) will be applied 20 minutes after induction of anesthesia, without RM in the control group (group C) and after RM in the recruitment group (group R). 
- Induction and maintenance of anesthesia will be done with propofol and remifentanil using target-controlled infusions (TCI).
- During surgery, a tidal volume of 6–8 mL/kg of predicted body weight, PEEP of 5 cmH2O, FIO2 of 0.4, inspiratory:expiratory ratio of 1:2, PIP less than 35 cmH2O in pressure control mode will be maintained, and RR will be adjusted to maintain ETCO2 of 35~40 mmHg. 
- Arterial blood gas analysis is going to be performed as baseline measurements before application of RM and PEEP (T1), 30 min after induction of CO2 pneumoperitoneum (T2), 90 min after induction of CO2 pneumoperitoneum (T3), and 30 min after arrival in the PACU in room air (T4) to assess oxygenation status.
- Pulmonary function tests will be done preoperatively and postoperatively to assess changes in pulmonary function after surgery, and chest CT scan will be done postoperatively to check lung complications, such as atelectasis.
- Exclusion criteria are as follows: overweight (BMI > 31 kg/m2), existing myocardial infarction, a history of cardiac disease, having a moderate or severe obstructive or restrictive pattern on pulmonary function testing, active pulmonary disease and heavy smoking, neuromuscular disease, having neurologic sequelae due to neurologic disease, dementia, and renal disease. 	
Principal researcher	[name], Department of Anesthesiology & Pain medicine	
Research period	1 year from IRB approval (assumed to be ~2014.8)	
Financial suppot	Research program of the Seoul National University Bundang Hospital	

Research proposal
1. Title
Effects of recruitment maneuver in patients undergoing robotic assisted radical prostatectomy

2. Institution
Seoul National University Bundang Hospital, Department of Anesthesiology & Pain medicine
[name]

3. Researchers
[name], Department of Anesthesiology and Pain Medicine, Seoul National University Bundang Hospital
[name], Department of Anesthesiology and Pain Medicine, Seoul National University Bundang Hospital
[name], Department of Anesthesiology and Pain Medicine, Chungnam National University Hospital
[name], Department of Anesthesiology and Pain Medicine, Seoul National University Bundang Hospital
[name], Department of Anesthesiology and Pain Medicine, Seoul National University Bundang Hospital
[name], Department of Anesthesiology and Pain Medicine, Seoul National University Bundang Hospital
4. Financial support
Research Program of the Seoul National University Bundang Hospital

5. Background 
5.1 Increasing demand for Robotic assisted radical prostatectomy(RARP)
- Robotic-assisted laparoscopic radical prostatectomy (RARP) has attracted increasing attention because it has lower rates of complications and improves the surgical outcome compared to open radical prostatectomy. [1, 2]
- In terms of anaesthetic management, RARP reduces blood loss, lowers the rate of transfusion, and shortens the hospitalisation period in comparison to conventional prostatectomy. [3]

5.2 Characteristics of RARP
- To facilitate RARP, the operative position should be a Trendelenburg head-down position as much as possible. 
- Therefore, the operative position for RARP has a 30¡Æslope, which is much steeper than that of other surgeries. 
- In addition, a relatively higher CO2 gas insufflation pressure, of up to 17 mmHg, is used to improve visualisation. 
- The steep Trendelenburg head-down position and relatively long duration of CO2 pneumoperitoneum (generally more than 3 hours) can result in an increased risk of intraoperative hypoxia and postoperative atelectasis [4, 5]. In addition, an increase of PaCO2 can be difficult to control. 
- Furthermore, patients undergoing RARP are mostly elderly and the likelihood of difficulty of management of intraoperative oxygenation, and the risk of postoperative pulmonary complications, are increased. 

5.3 Measures for preventing atelectasis and improving oxygenation during general anesthesia
- Atelectasis develops after the induction of general anaesthesia due to mechanical ventilation in 90% of patients [6]. 
- To prevent postoperative atelectasis and to improve oxygenation, positive end expiratory pressure (PEEP), maintenance of muscle tone, recruitment manoeuvre (RM), and minimisation of absorption of gas can be used [7]. 

5.4 Application of PEEP and RM in RARP
- RM is an important component of lung-protective ventilation, which has proven to be beneficial in the ventilation of patients with acutely diseased lungs, such as those with acute respiratory distress syndrome or asthma [8]. 
- PEEP and RM both can be used in RARP to improve oxygenation.
- PEEP can be applied during surgery constantly.
- RM is expected to improve oxygenation during surgery, but whether RM is effective in RARP is yet to be proven. Especially due to steep trendelenburg head down position and relatively long duration of CO2 pneumoperitoneum, it is hard to predict how much effect RM will have or whether RM can influence postoperative lung care. 

5.5 Pre-existing studies
- In RARP, regarding ventilatory management there are only studies about the difference between volume controlled mode and pressure controlled mode or whether PEEP improves oxygenation during surgery. [9, 10]

5.6 Research objective
- This study was designed to evaluate the efficacy of RM in addition to PEEP on intraoperative oxygenation, ventilatory mechanics, and perioperative pulmonary complications in patients undergoing RARP. 

6. Subjects
   Patients undergoing elective RARP under general anesthesia

7. Research period
  1 year from IRB approval (assumed to be ~2014.8)

8. Recruiment of participants
8.1. Inclusion and exclusion criteria
Inclusion criteria
¨ç age 60-80 years 
¨è ASA class 1, 2 
¨é scheduled for RARP under general anesthesia
¨ê written informed consent

Exclusion criteria
¨ç history of myocardial infarction 
¨è valvular heart disease
¨é moderate or severe obstructive or restrictive pattern on pulmonary function testing
¨ê heavy smoker
¨ë neurologic sequelae due to neurologic disease
¨ì renal insufficiency
¨í overweight (BMI > 31 kg/m2)

Dropout criteria
Patient¡¯s refusal to participate 
Change in surgical plan to other procedure than RARP
Patients whose saturation decrease below 95%, or PaCO2 exceed 7.3 kPa 

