10.3. Ramdomisation
Before registration of participants, a block assign list according to the random number table will be made, which consists of blocks sized 4 which contains 2 patients from control group(A) and 2 patients from experimental group(B) (AABB, BBAA, ABAB, BABA, ABBA, BAAB), and blocks sized 6 which contains 3 patients from each group (AAABBB, AABABB, AABBAB, AABBBA, BBBAAA, BBABAA, BBAABA, BBAAAB, ABAABB, ABABAB, ABABBA, ABBBAA, ABBAAB, ABBABA, BAAABB, BAABAB, BAABBA, BABBAA, BABABA, BABAAB). The participants will be assigned to control group and experimental group according to this random assign list. 
All the process of randomisation will be conducted by an anesthesiologist who is not involved in the study, and the assignment will be kept in a sealed envelope which is not accessible to the researchers until induction of anesthesia. 

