10.5. Study protocol
All the clinical procedures other than RM will be conducted in same measures in both group.
- The patients who are undergoing elective RARP under general anesthesia will be enrolled.
- The participants will be randomly allocated into 2 groups.
- After induction, 5 cmH2O of PEEP will be applied to all patients without RM in the control group (group C) and after RM in the recruitment group (group R). 
-	Participants will be premedicated with 2 mg of midazolam.
- Induction and maintenance of anesthesia will be done with propofol and remifentanil using an Orchestra infusion pump system (Fresenius Vial, Brezins, France). The concentrations of propofol and remifentanil wil be adjusted with TCI to maintain a bispectral index (BIS) of 40–60 (measured with an A-2000 BISTM monitor; Aspect Medical Systems Inc., Natick, MA, USA). 
- Muscle relaxation will be done before tracheal intubation using 0.6 mg/kg of rocuro nium.
- During surgery, a tidal volume of 6–8 mL/kg of predicted body weight, PEEP of 5 cmH2O, FIO2 of 0.4, inspiratory:expiratory ratio of 1:2, PIP less than 35 cmH2O in pressure control mode will be maintained, and RR will be adjusted to maintain ETCO2 of 35~40 mmHg. 
- Lungs are going to be recruited by increasing the PEEP gradually, from 4 cmH2O (2 breaths) to 6 cmH2O (2 breaths), 8 cmH2O (2 breaths), and finally 16 cmH2O (10 breaths). After 10 breaths with 16 cmH2O, PEEP is going to be decreased stepwise as before. 
- The surgical procedure will be conducted using robotic sytem(da Vinci; Intuitive Surgicla, Inc., Sunnyvale, CA), and intraabdominal pressure of 17 mmHg will be maintained during the procedure.
- During the intraoperative and PACU periods, arterial blood gas analyses will be performed as baseline measurements before application of RM and PEEP (T1), 30 min after induction of CO2 pneumoperitoneum (T2), 90 min after induction of CO2 pneumoperitoneum (T3), and 30 min after arrival in the PACU in room air (T4). 
- The patient-tested baseline pulmonary function testing will be performed using a portable spirometer (MicroLoop¢â; Carefusion, Basingstoke, UK) on a day before operation, before leaving the post-anaesthetic care unit (PACU), and on the postoperative second day. 

- Low-dose chest computed tomography (CT) will be performed on the postoperative second day for evaluation of postoperative atelectasis. 

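### The dropout criterion on saturation below 95% acts after randomisation on an outcome that RM is expected to change, and the protocol implies that such patients leave the analysis

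*Protocol*

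**What the plan says.** Section 8.1 of the protocol has three lists: inclusion, exclusion and dropout criteria. The third contains refusal, a change to another operation, and "Patients whose saturation decrease below 95%, or PaCO2 exceed 7.3 kPa". No time window, inspired oxygen condition or study group is attached to this last line.

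Under 10.3 the list is drawn up in advance and "the assignment will be kept in a sealed envelope which is not accessible to the researchers until induction of anesthesia". The Summary of proposal puts PEEP, preceded by RM in group R, 20 minutes after induction. Section 10.5 takes blood gases before RM and PEEP (T1), 30 and 90 minutes into the pneumoperitoneum (T2, T3), and in the PACU on room air (T4). The low-dose CT for atelectasis and the last spirometry are on the second postoperative day.

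The objective in 5.6 is the "efficacy of RM in addition to PEEP on intraoperative oxygenation, ventilatory mechanics, and perioperative pulmonary complications". Section 5.4 adds that "RM is expected to improve oxygenation during surgery". The primary outcome (10.4, 10.7) is the incidence of perioperative pulmonary complications. Section 10.4 assumes a 30% incidence, a 90% reduction, 80% power, a two-sided 5% level and 20% dropouts, and arrives at 30 per group.

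**The concern.** A rule that removes patients for something measured after allocation is harmless only if it is unrelated to treatment and outcome. Here the trigger is saturation, which the protocol expects RM to improve. If RM does so, fewer patients in group R cross the limit than in group C. Those who cross are probably also more likely to show atelectasis on the day-2 CT, and they would have left before it.

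The comparison would then be made among patients selected by a consequence of treatment, and randomisation would no longer protect it. This affects the primary incidence. It also affects the intraoperative blood gases and compliance, because the patients with the poorest oxygenation are the ones taken out. If RM works, the expected bias is towards no difference; if RM itself caused desaturation, more patients would leave group R instead.

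**Working it through.** **1. The plan's own figure.** Inputs from 10.4: 30% in controls; 30% × (1 − 0.90) = 3% with RM; two-sided 5%; 80% power; 20% dropouts. The arcsine formula has h = 2·asin(√0.30) − 2·asin(√0.03) = 0.811 and n = 2 × ((1.960 + 0.842)/0.811)² = 23.9, so 24 per group. Then 24/(1 − 0.20) = 30. The stated number reproduces, and it shows how 10.4 treats dropouts: 30 are randomised so that 24 can be analysed.

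Exact power of the uncorrected chi-square test at 30% vs 3% is 80% with 24 per group and 88% with 30 per group.

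**2. Is anyone retained?** Sections 10.4, 10.7 and 10.9 name no analysis population, do not count a crossing as an outcome, and do not ask for the CT in patients who have dropped out.

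**3. Illustration A: the same rule in both groups.** The protocol gives no crossing rates, so these are assumed. Let q1 be the share of patients with a complication who cross the limit, and q0 the share of those without. For a true incidence p:

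- dropout d = p·q1 + (1 − p)·q0
- observed incidence = p(1 − q1)/(1 − d)
- number analysed = 30(1 − d), rounded

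Example with q1 = 30% and q0 = 5%:

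- Group C: d = 0.30 × 0.30 + 0.70 × 0.05 = 0.125; observed 0.30 × 0.70/0.875 = 24.0%; n = 26.
- Group R: d = 0.03 × 0.30 + 0.97 × 0.05 = 0.0575; observed 0.03 × 0.70/0.9425 = 2.2%; n = 28.

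| q1 / q0 (assumed) | Dropout C vs R | Observed C vs R | Difference (true: 27 points) | Exact power |
|---|---|---|---|---|
| 20% / 5% | 9.5% vs 5.4% | 26.5% vs 2.5% | 24.0 | 79% |
| 30% / 5% | 12.5% vs 5.8% | 24.0% vs 2.2% | 21.8 | 72% |
| 50% / 5% | 18.5% vs 6.4% | 18.4% vs 1.6% | 16.8 | 51% |
| 50% / 10% | 22.0% vs 11.2% | 19.2% vs 1.7% | 17.5 | 51% |

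**4. Illustration B: a fixed share of controls drops out.** Assume that 60% of dropped controls would have had a complication, and that 2% of group R drop out, 30% of them with one. Observed control incidence is (0.30 − 0.6d)/(1 − d). In group R it is (0.03 − 0.02 × 0.3)/0.98 = 2.4%, with 29 analysed.

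- d = 5%: 0.27/0.95 = 28.4%, n = 28, power 86%
- d = 10%: 0.24/0.90 = 26.7%, n = 27, power 80%
- d = 20%: 0.18/0.80 = 22.5%, n = 24, power 73%

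For comparison, losing the same numbers at random (24 vs 29 analysed, still 30% vs 3%) leaves 86%. In the 20% case, most of the fall from 88% to 73% therefore comes from who is lost and not from how many.

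**The case against.** The strongest defence is that removal from the analysis is inferred. Section 8.1 says dropout; it does not say that these patients are left out of the analysis or refused the CT, and a statistical analysis plan not shown may name an as-randomised population. This stands as a limit on certainty. It does not answer the point, because 10.4 counts dropouts as lost, and no later analysis rule can supply a CT that was never taken.

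Several stronger readings are tempting but not supported:

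- **That both limits are events RM is meant to prevent.** Only oxygenation is tied to RM. For PaCO2, 5.2 says merely that a rise may be hard to control, and respiratory rate is adjusted to the same end-tidal target in both groups. This part is secondary.
- **That the protocol expects these events.** Section 5.2 speaks only of a raised risk of hypoxia during surgery and of a PaCO2 that may be hard to contain. That is a risk without a frequency.
- **That every crossing reflects treatment.** A crossing at T1 precedes RM. Application to the room-air reading at T4 follows from the missing time window and is not stated.
- **That the change-of-surgery criterion has the same fault.** Nothing links RM to a change of operation.
- **That the damage cannot be repaired.** This holds only if follow-up stops at dropout.
- **That power falls to 48%.** That figure puts the whole any-cause 20% allowance on group C and treats every dropped patient as a primary event: (0.30 − 0.20)/0.80 = 12.5% in controls and (0.03 − 0.02)/0.98 = 1.0% in group R. The protocol neither splits the allowance by group nor says whether desaturation is a pulmonary complication.

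It is also fair that the plan budgeted for 24 analysed per group, with 80% exact power. With 5% to 10% of controls lost, power is no lower than that.

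**Conclusion.** The point holds for the saturation limit, with PaCO2 secondary. As written, the protocol fixes a post-randomisation dropout rule on a variable that RM is expected to change, and it does not separate stopping study procedures from leaving the trial's data. Loss from the analysis is implied, not stated.

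The size is illustrative. In the Illustration A scenarios, dropout is unequal between groups and the observed difference shrinks by about 3 to 10 points. Exact power ranges from about 79% down to 51%, against 88% with everyone analysed. Light control dropout (Illustration B, 5% to 10%) leaves about 86% to 80%. All of this assumes the plan's 30% vs 3%, that RM works, and that patients with a complication cross the limit more often than those without. The case for changing the rule does not depend on any one of these rates: it compromises the randomised comparison by an amount that cannot be known in advance.

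**What to change.** Leave the clinical threshold and the management of these patients as they are; neither is judged here. Add to 8.1 that crossing the threshold, or any other stop of study procedures, does not remove the patient from follow-up or analysis. Collect the already planned day-2 CT and spirometry in every randomised patient unless consent is withdrawn. State in 10.9 that patients are analysed in the group to which they were randomised. Report saturation and PaCO2 crossings by group and time point, so that those at T1 can be told apart from those after RM.

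The cost is protocol wording; no extra patients or new procedures are needed. The downside is that patients who received additional treatment stay in the comparison, which slightly dilutes the ventilatory contrast.

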10.4. Sample size
  The primary outcome is the incidence of perioperative pulmonary complications. Sample size calculation was based on a previous study in which the incidence of atelectasis after laparoscopic surgery was 30% [11]. We considered a reduction of the incidence by 90% to be statistically significant. Thus, we calculated that 30 patients would be needed in each group, using a two-sided test with 80% power and a 5% ¥á-error, allowing for 20% dropouts. 

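### Desaturation or hypercapnia is a dropout criterion that can act after allocation, which puts the primary and gas-exchange comparisons at risk of outcome-dependent exclusion

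*Protocol*

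**What the plan says.** Protocol 8.1 has three dropout criteria, listed apart from the exclusion criteria: refusal, a change to another operation, and "Patients whose saturation decrease below 95%, or PaCO2 exceed 7.3 kPa". The third gives no time point, duration or FIO2.

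On timing, 10.3 says that "the assignment will be kept in a sealed envelope which is not accessible to the researchers until induction of anesthesia". Under 10.5 the first planned arterial sample (T1) is an intraoperative baseline before RM and PEEP. T2 and T3 fall during pneumoperitoneum, and T4 is in the PACU on room air. FIO2 during surgery is 0.4.

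On purpose, 5.6 sets out to study the "efficacy of RM in addition to PEEP on intraoperative oxygenation, ventilatory mechanics, and perioperative pulmonary complications". Section 5.4 expects RM to improve oxygenation. Section 10.7 makes the incidence of perioperative pulmonary complications the primary outcome and lists blood-gas results among the other variables. Section 5.2 anticipates intraoperative hypoxia and adds that "an increase of PaCO2 can be difficult to control".

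On numbers, 10.4 assumes 30% atelectasis, a 90% reduction, two-sided 5% alpha and 80% power, and arrives at 30 per group "allowing for 20% dropouts". Section 10.8 assesses safety in all included patients.

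**The concern.** Saturation and PaCO2 measured after allocation are results of treatment. If crossing a limit removes a randomised patient, and RM does what 5.4 expects, more control patients than RM patients will cross. The control group then loses more of its patients with poor gas exchange, who are plausibly also those more likely to have atelectasis on the day-2 CT. The groups left for comparison are no longer the groups that were randomised.

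Two sets of comparisons are exposed. The primary comparison loses likely events, disproportionately from the control group. The blood-gas comparisons lose their worst values, because the rule cuts directly on saturation and PaCO2. In both, the likeliest effect is to shrink a real difference in favour of RM.

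The 20% allowance protects power only against loss unrelated to outcome. It does not address this kind of loss.

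**Working it through.** **1. When the rule can act.** The envelope may be opened at induction (10.3), and the first planned blood gas comes after induction (10.5). At the planned samples, the PaCO2 limb can therefore act only after allocation. The saturation limb has no time point, so the text does not confine it to any period. A drop at T1 precedes RM and cannot reflect its effect; a drop from T2 onward can.

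**2. The protocol's own sample size.** Inputs from 10.4: p_C = 0.30, p_R = 0.30 × (1 − 0.90) = 0.03, two-sided alpha 0.05, power 0.80. The method is not named. The arcsine formula gives

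h = 2·asin(√0.30) − 2·asin(√0.03) = 1.159 − 0.348 = 0.811

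n = 2 × [(1.960 + 0.842)/0.811]² = 23.9, rounded up to 24; 24/(1 − 0.20) = 30.

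This matches the stated 30. The sizing thus treats 24 per group as evaluable and dropouts as contributing nothing. Exact enumeration of the uncorrected chi-square test gives power of 80.0% at 24 per group and 88.4% at 30 per group.

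**3. Dropout related to outcome (assumed rates).** Let d_A and d_N be the dropout probabilities with and without atelectasis, the same in both groups. Then

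proportion retained = p(1 − d_A) + (1 − p)(1 − d_N)

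observed rate = p(1 − d_A) / proportion retained.

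For d_A = 0.5 and d_N = 0.1: C = 0.15/0.78 = 19.2%; R = 0.015/0.888 = 1.7%. Power is by exact chi-square at the expected numbers retained out of 30, rounded.

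| d_A / d_N | Dropout C v R | Observed C v R | Power |
|---|---|---|---|
| none | 0% v 0% | 30% v 3% | 88% |
| 10% / 5% | 6.5% v 5.2% | 28.9% v 2.8% | 85% |
| 20% / 5% | 9.5% v 5.5% | 26.5% v 2.5% | 79% |
| 50% / 10% | 22% v 11% | 19.2% v 1.7% | 51% |
| 80% / 10% | 31% v 12% | 8.7% v 0.7% | 23% |

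The last two powers are sensitive to rounding. Averaging over a binomial number retained gives 58% and 18%; the first two dropout rows become 84% and 80%.

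**4. Control dropout held at the protocol's 20%.** Pooled-normal power, which runs lower than the exact figures:

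- Loss unrelated to outcome: 30% v 3%, power 73%.
- d_A/d_N = 40%/11.4%: 22.5% v 2.1%, power 61%; dropout 20% v 12%.
- 50%/7.1%: 18.7% v 1.6%, power 55%; dropout 20% v 8%.
- 67%/0%: 12.5% v 1.0%, power 42%; dropout 20% v 2%.

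**5. RM changes threshold crossing but not atelectasis.** Take 30% atelectasis in both groups, with d_A/d_N of 50%/10% in C and 20%/5% in R. Retained rates are C = 0.15/0.78 = 19.2% and R = 0.24/0.905 = 26.5%, a shift against RM. At 23 v 27 patients, chi-square rejects about 8.6% of the time (both directions together) against a nominal 5%.

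**6. Blood gases.** The direction follows from cutting off the worst values. The protocol gives no expected means or standard deviations, so no size is calculated.

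**The case against.** The strongest reply is that the protocol never says dropped patients lose follow-up or leave the analysis. The 20% allowance is ordinary inflation that also covers refusal and a change of operation, and a statistical analysis plan that is not shown could define the analysis set. This stands in part: removal is implied, not stated. But the protocol itself fixes the criterion. If dropping a patient means no day-2 CT or spirometry, no later analysis set can recover those data.

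The size is also open to challenge. The severe rows in step 3 exceed the 20% allowance in the control group, and the milder rows leave power near or above 80%. That stands, and the honest range runs from negligible to severe. Step 4 shows that the loss can still be substantial with control dropout held at 20%.

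A reader might infer more than the text supports:

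- **That every comparison is biased.** Safety covers all included patients, a drop at T1 cannot reflect RM, and there is no bias in the primary comparison if crossing is unrelated to that outcome.
- **That the rule would reverse the primary result.** Step 5 shows a shifted estimate that would rarely be significant.
- **That a dropped hypoxic event is itself a primary-outcome event.** The protocol does not list the components of that outcome.
- **That the 95% limit definitely applies on room air at T4.** With no time point given, that is one reading.

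**Conclusion.** The concern holds for the primary pulmonary-complication comparison and the gas-exchange comparisons. As written, 8.1 allows randomised patients to be dropped on variables that RM is expected to change, and the sizing in 10.4 implies that they are not analysed. The likeliest consequence is a diluted RM effect.

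The size cannot be determined from the protocol. Against 88% power with everyone analysed, the assumed scenarios run from about 85% (10%/5% dropout with/without atelectasis) to about 23% (80%/10%). These figures assume that the planned 30% v 3% is true, that 30 are randomised per group, and that crossing a limit leads to removal from the analysis. The point should be settled before enrolment, because follow-up not obtained cannot be restored.

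**What to change.** Amend 8.1 to separate any stopping of protocol ventilation from leaving the study:

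- State that crossing either limit is not a reason to leave follow-up or the analysis.
- State that these patients have all later planned blood gases, spirometry and the day-2 CT, and are analysed in their randomised group.
- Record each crossing with its time and FIO2, and report crossings by group.
- Keep the 20% allowance in 10.4 for patients with no primary-outcome data.

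The clinical response at these values stays with the investigators; the change concerns follow-up and analysis only.

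The cost is a short amendment and a line on the case report form, with no additional patients or procedures beyond those already planned. Some retained patients will have had changed ventilation or oxygen, which slightly dilutes a comparison under protocol ventilation. A sensitivity analysis can show how much this matters.
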